### Blinding

The repellent and lotion were labelled by the manufacturers with a 3-digit code, and will reveal which is which at the end of trial. The trial staff and local health staff carrying out randomisation and surveys are therefore blinded to the treatment arms. Participants were informed as part of the recruitment process that they had an equal chance of receiving the placebo or repellent. The possibility does remain of participants being able to distinguish the DEET lotion from the placebo by a slight difference in smell.

### Interventions

All participants will be provided with and sleep under long-lasting insecticide treated nets (LLINs) every night (PermaNet®2.0, deltamethrin 55mg/m2, mesh 25 holes/cm2). A 15% DEET lotion will be provided to half the households the other half of households will receive a placebo lotion (both supplied by SCJohnson). Adult participants will be provided with three 50ml bottles of their lotion to last one month (approximately 5ml per day). Children under 12 years will be provided with two bottles per month, corresponding to approximately 3ml per day. These exposures, based on Antwi *et al.* (2008), would have margins of exposure greater than 100 (exposure is less than 1% of NOEL) for acute and chronic toxicity. District health staff will demonstrate the amount of lotion to apply to arms and legs during the recruitment process. Participants are instructed to use the lotion every evening, but are free to also use the lotion during the day if desired.

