### Potential Risks and Benefits

Finger-prick blood spots do cause modest, brief discomfort but are common in use in this area and it is likely most individuals will have already experienced this. Risk from this procedure is very low and antiseptic wipes are used to prevent infection.

Use of repellent is universal worldwide and present extremely low risk. We are using a high quality commercial brand made, registered and sold in the USA by SC Johnson. We are using the lowest effective dose of active 15% DEET and a consumer friendly gentle aqueous lotion formulation to minimise risk and discomfort. As young children have a lower body volume / skin surface ratio we will not enrol anyone under six years old. Full USA compliant consumer product information will be given verbally and in local language on the products. Any contraindications or side effects will be recorded and reported for appropriate action to local District Health departments. All positive cases will be referred for immediate treatment following local guidelines through the District Health teams working with us on the study. Treatment for *P. falciparum* with co-artem is free at the point of delivery in Lao PDR.

If findings are positive there would be a strong case for the use of repellents as part of future vector-borne disease control programmes.

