## PARTICIPANT AND HOUSEHOLD ELIGIBILITY

Participants will be on primarily recruited amongst rural agricultural workers that often work and sleep overnight away from the village during the wet season. Households must enrol at least five eligible participants to enter the trial. Participants must be aged 6-60 years to take part in the trial.

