### Recruitment and Baseline Survey

Recruitment will take place in May 2009, when 300 households will be recruited from Attapeu province, and in April 2010, when 1,300 households will be recruited from both Attapeu and Sekong provinces. Participants will be recruited as volunteers from meetings with village members and local health team staff where the study will be described in full with opportunity for questions. Individuals that wish to take part will also receive this information in writing and sign a consent form to confirm they understand the trial, including the possibility they may receive the placebo lotion. A maximum of 25% of households will be recruited from any village in order to overcome diversion of bites to non-repellent users. In addition district health staff will be responsible for ensuring that study houses contain at least five eligible participants (if the household is bigger, more can be recruited), and that study houses are distributed throughout the village, the rule being that study houses should be a minimum of 10m apart. The baseline survey is scheduled for the same time as recruitment, May 2009 and April 2010. The questionnaire, estimated to take 30 minutes, will collect basic information on wealth indicators and current malaria prevention behaviour for the household and individual information on malaria exposure.

Households will be randomly assigned to one of the treatment groups and supplied with three 100ml bottles per person per month to allow for 10ml use per day as well as sufficient LLINs for the whole household, including non-participants (sufficient LLINs defined as one net for every 1.5 persons in the household, plus another for use away from home). District health staff will demonstrate how to use the lotion and explain that it should be used every evening. Participants will also be encouraged to use the lotion during the day if they notice biting.

A bloodspot will also be taken from each participant and stored on filter paper for laboratory analysis for dengue, JE and typhus. Analysis will ideally take place in Laos if facilities can be found, but if this is not possible the bloodspots will be transported to the UK or France for testing.

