## SAFETY CONSIDERATIONS

### DEET Safety

DEET was first registered for use as an insect repellent over 50 years ago; it is effective against a wide range of insects and still remains the most widely used repellent today, with an estimated 200 million annual applications (Barnard 2000). However, DEET has been linked to adverse events following high exposures, primarily involving seizures and encephalopathy in children (Osimitz and Grothaus 1995). Qiu *et al.* (1998) reviewed the safety of DEET and found the compound associated with cases of encephalopathy, seizures and dermatitis; however concluded that DEET was safe when used appropriately given that the incidence of adverse effects was very low when its widespread use was considered.

About 5-8% of applied DEET is absorbed into the skin, but is subsequently completely metabolised and mostly excreted in the urine within four hours (Selim *et al.* 1995). Veltri *et al.* (1994) reviewed over 9,000 calls to American Poison Control Centres involving DEET exposure. Over half of exposures had no symptoms at the time of the call, and symptoms usually occurred through inhalation or contact with eyes. Almost 90% of exposures were treated solely at home, and 80% of those referred to a health centre were discharged after initial examination, suggesting mild or short-lived symptoms. Severity of symptoms was more closely related to the type of exposure than the concentration of DEET, or the age or gender of the patient. The United States Environmental Protection Agency reviewed DEET safety and concluded that it was not possible to identify DEET as the cause of seizures or encephalopathy and that there was no unreasonable risk to human health when used according to product instructions (USEPA 1998).

The safety of DEET use in pregnant women was assessed during a clinical trial of the product for the prevention of malaria (McGready *et al.* 2001b). No adverse neurological, gastrointestinal or dermatological effects were reported and neither were there any adverse effects on survival or development of the babies at birth or one year. Antwi *et al.* (2008) carried out a risk assessment of DEET use by humans. Based on animal tests a no-observed-effect-level (NOEL) was set at 200 mg DEET per kg body weight for acute toxicity, and 500 mg DEET per kg body weight dose per day was set for chronic toxicity.

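### The protocol gives two conflicting lotion supplies, and the stated safety margin covers only the smaller one

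*Protocol*

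**What the plan says.** Two sections of the protocol describe how much lotion participants receive.

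- **Interventions.** For adults: "Adult participants will be provided with three 50ml bottles of their lotion to last one month (approximately 5ml per day". For children: "Children under 12 years will be provided with two bottles per month, corresponding to approximately 3ml per day". The next sentence refers to these amounts, cites a published risk assessment, and claims "margins of exposure greater than 100 (exposure is less than 1% of NOEL) for acute and chronic toxicity".
- **Recruitment and Baseline Survey.** Households are randomised and then "supplied with three 100ml bottles per person per month to allow for 10ml use per day". The allowance is per person, with no separate figure for children. The same paragraph adds: "Participants will also be encouraged to use the lotion during the day if they notice biting".

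Three other statements bear on the point. Eligibility: "Participants must be aged 6-60 years to take part in the trial". Potential Risks and Benefits: "As young children have a lower body volume / skin surface ratio we will not enrol anyone under six years old". DEET Safety gives an acute figure ("NOEL) was set at 200 mg DEET per kg body weight for acute toxicity"), a chronic figure of 500 mg/kg per day, and dermal absorption of roughly 5-8%.

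No section restates the margin for 10 ml/day, says which supply governs, or assigns the two supplies to different years. The recruitment section covers both the 2009 and the 2010 intake.

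**The concern.** The claimed margin is the only quantitative exposure margin in the protocol, and it is tied to specific volumes. The reduced child volume is part of what supports it. A second section then describes a larger supply for the same trial and drops the child reduction, although the protocol elsewhere excludes under-sixes on grounds of body size.

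Staff who follow the recruitment section would issue lotion to children from age six at a level the stated margin was not given for. An ethics committee reading the Interventions section would believe exposure stays below 1% of the NOEL. There is also a practical cost. Quality Control and Assurance uses the lotion left in returned bottles as an indirect measure of use, and that cannot be interpreted without knowing the volume issued.

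**Working it through.** **1. The two supplies**

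| | Interventions | Recruitment section | Ratio |
|---|---|---|---|
| Adult | 3 × 50 = 150 ml/month, 5 ml/day | 3 × 100 = 300 ml/month, 10 ml/day | 2 |
| Under 12 | 2 × 50 = 100 ml/month, 3.3 ml/day (given as about 3) | 300 ml/month, 10 ml/day | 3 |

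The child row reads the two bottles as 50 ml each, which agrees with the stated 3 ml or so a day. The ratios need no toxicological assumption. If the margin is inversely proportional to dose, then on any basis the margin at the Interventions volumes would have to exceed 200 for adults and about 300 for children for a figure above 100 to survive at 10 ml/day. The protocol claims only more than 100.

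**2. Inputs for the illustration**

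- From the protocol: 15% DEET; 5-8% absorbed; NOEL 200 mg/kg acute and 500 mg/kg per day chronic.
- Assumed: 15% taken as 150 mg/ml; body weights; margin calculated on absorbed dose; the whole daily allowance used.

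Margin = NOEL ÷ (ml per day × 150 × absorbed fraction ÷ body weight in kg)

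**3. Reproducing the protocol's figure at its own volumes**

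- 60 kg adult, 5 ml: 750 mg applied, 37.5-60 mg absorbed, 0.625-1.0 mg/kg. Acute 200/1.0 to 200/0.625 = 200-320. Chronic 500-800.
- 20 kg child, 3 ml: 450 mg applied, 22.5-36 mg absorbed, 1.125-1.8 mg/kg. Acute 111-178. Chronic 278-444.
- The same child at the unrounded 3.33 ml: 500 mg applied, 25-40 mg absorbed, 1.25-2.0 mg/kg. Acute 100-160.

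The claim broadly reproduces. At 8% absorption the acute margin reaches 100 at 18 kg on 3 ml, 20 kg on 3.33 ml and 30 kg on 5 ml, so it slips below 100 only for people lighter than that. Without the absorption factor the acute margin would be 200 ÷ (750/60) = 16 for the adult and 200 ÷ (450/20) = 8.9 for the child on 3 ml. Absorbed dose is therefore the basis that fits the claim, though the protocol does not state it.

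**4. The same calculation at 10 ml/day**

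10 × 150 = 1,500 mg applied; 75-120 mg absorbed.

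| Assumed weight | Absorbed dose (mg/kg) | Acute margin | Chronic margin |
|---|---|---|---|
| 20 kg | 3.75-6.0 | 33-53 | 83-133 |
| 30 kg | 2.5-4.0 | 50-80 | 125-200 |
| 50 kg | 1.5-2.4 | 83-133 | 208-333 |
| 60 kg | 1.25-2.0 | 100-160 | 250-400 |

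For the 20 kg child, 3.75/200 to 6.0/200 is 1.9-3.0% of the acute NOEL, against the stated figure of under 1%.

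**5. Dependence on the assumed weight**

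An acute margin of 100 allows 200/100 = 2 mg/kg. At 10 ml/day that needs at least 75/2 = 37.5 kg at 5% absorption, or 120/2 = 60 kg at 8%. Below 37.5 kg the acute margin is under 100 throughout the absorption range.

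**The case against.** The strongest reply is that the Interventions sentence is not wrong. It attaches the margin to its own volumes, where the figure broadly holds. **That stands.** A reader might infer an arithmetic error there, or a fault in the cited risk assessment. The documents support neither: the figure reproduces on a plausible basis, and the assessment's method is not shown.

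Second, the illustration is a reviewer's construction. Body weight appears nowhere in the protocol, 150 mg/ml assumes a density, and the absorption range comes from a different cited study than the NOELs. **This also stands.** The 33-53 is conditional and should not be presented as the protocol's own figure. The twofold and threefold ratios do not depend on it.

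Third, supply is not use. Staff demonstrate the amount to apply, bottles are returned monthly, and 10 ml is a ceiling. The acute figure also counts a full day's allowance as a single dose, although DEET Safety says absorbed DEET is mostly excreted within four hours. So 10 ml/day is properly an upper bound. **The reply does not remove the point**, because the recruitment section names 10 ml as the use it allows for, and the Interventions exposures are themselves derived from bottles supplied.

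A reader might also take the encouragement of daytime use to mean exposure beyond 10 ml/day. The text does not say so: daytime use comes from the same bottles, and the Interventions section permits it too. Nor does a margin below 100 show that children would be harmed. The rest of the safety case (a registered product, exclusion of under-sixes, the pregnancy trial, the regulator's review) is untouched.

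**Conclusion.** The point holds as a contradiction between two sections, with a safety statement that covers only one of them. The contradiction is certain from the text: 10 ml/day against about 5 ml (adults) and about 3 ml (under-12s), with no child reduction in the larger supply.

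The size of the shortfall is conditional on 150 mg/ml, an absorbed-dose basis at 5-8%, and full use of the allowance. On those terms the clear failure is the acute margin for participants under 37.5 kg. The chronic margin at 20 kg and the acute margin at 50 kg both straddle 100. Only the DEET arm is concerned, and no endpoint, power figure or analysis changes. It is worth correcting because the discrepancy concerns the dose given to children and is cheap to remove.

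**What to change.** Decide which supply is intended, then do one of the following.

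- **If the Interventions volumes are intended:** correct the Recruitment and Baseline Survey section to 150 ml a month for adults and two 50 ml bottles for under-12s. The margin statement can then stay.
- **If 10 ml/day is what is supplied:** withdraw the claim of more than 100 from the Interventions section, and state the lower margin that applies at 10 ml/day, for children as well as adults, with the basis on which it is calculated.

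The first option costs a correction to one paragraph. The second adds a short recalculation and a less favourable stated margin, clearly lower for children. Either way the ethics committees should be notified.

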## PARTICIPANT AND HOUSEHOLD ELIGIBILITY

Participants will be on primarily recruited amongst rural agricultural workers that often work and sleep overnight away from the village during the wet season. Households must enrol at least five eligible participants to enter the trial. Participants must be aged 6-60 years to take part in the trial.

## STUDY PROCEDURES AND EVALUATIONS

### Study Schedule

| Activity | 2009 | 2010 |
| --- | --- | --- |
| Design of consent form and survey forms | March | - |
| Design of database | March | - |
| Recruitment and training of Trial Coordinator | April | - |
| Design and approval of bi-lingual labels for lotions | April | - |
| Study design and SOPs approved by PSI and LSHTM | April | - |
| Translation of survey forms | April and May | - |
| Import and delivery of lotions, LLINs and RDTs | April-June | March-April |
| Gain ethics approval from LSHTM and Lao Ministry of Health | May | - |
| Training of District Health Staff | May-July & December | March-May & December |
| Selection of study villages | June | March |
| Training of VHVs | June, July & December | April, May & December |
| Recruitment and Baseline Surveys | June | April |
| Monthly follow-up Surveys | July-November | May-November |
| Evening spot checks | July-November | May-November |
| Entomology survey | July | July |
| Exit Survey | December | December |

### Recruitment and Baseline Survey

Recruitment will take place in May 2009, when 300 households will be recruited from Attapeu province, and in April 2010, when 1,300 households will be recruited from both Attapeu and Sekong provinces. Participants will be recruited as volunteers from meetings with village members and local health team staff where the study will be described in full with opportunity for questions. Individuals that wish to take part will also receive this information in writing and sign a consent form to confirm they understand the trial, including the possibility they may receive the placebo lotion. A maximum of 25% of households will be recruited from any village in order to overcome diversion of bites to non-repellent users. In addition district health staff will be responsible for ensuring that study houses contain at least five eligible participants (if the household is bigger, more can be recruited), and that study houses are distributed throughout the village, the rule being that study houses should be a minimum of 10m apart. The baseline survey is scheduled for the same time as recruitment, May 2009 and April 2010. The questionnaire, estimated to take 30 minutes, will collect basic information on wealth indicators and current malaria prevention behaviour for the household and individual information on malaria exposure.

Households will be randomly assigned to one of the treatment groups and supplied with three 100ml bottles per person per month to allow for 10ml use per day as well as sufficient LLINs for the whole household, including non-participants (sufficient LLINs defined as one net for every 1.5 persons in the household, plus another for use away from home). District health staff will demonstrate how to use the lotion and explain that it should be used every evening. Participants will also be encouraged to use the lotion during the day if they notice biting.

A bloodspot will also be taken from each participant and stored on filter paper for laboratory analysis for dengue, JE and typhus. Analysis will ideally take place in Laos if facilities can be found, but if this is not possible the bloodspots will be transported to the UK or France for testing.

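### The protocol gives two incompatible lotion supplies, and its safety margin covers only the smaller one

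*Protocol*

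**What the plan says.** The protocol states the lotion supply in two places.

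- **Interventions:** "Adult participants will be provided with three 50ml bottles of their lotion to last one month (approximately 5ml per day"). For the younger group, "Children under 12 years will be provided with two bottles per month, corresponding to approximately 3ml per day". The section then says that these exposures, on the basis of a cited risk assessment, "would have margins of exposure greater than 100 (exposure is less than 1% of NOEL) for acute and chronic toxicity".
- **Recruitment and Baseline Survey:** after random assignment, households are "supplied with three 100ml bottles per person per month to allow for 10ml use per day". No separate amount is given for children and no safety margin is stated. The section adds: "Participants will also be encouraged to use the lotion during the day if they notice biting".

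The DEET Safety section supplies the toxicological reference points: no-observed-effect levels (NOEL) of 200 mg/kg (acute) and 500 mg/kg/day (chronic). The same section notes that "DEET has been linked to adverse events following high exposures, primarily involving seizures and encephalopathy in children".

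**The concern.** The two sections cannot both be followed. Bottle size, daily allowance and the treatment of children all differ. Neither amount is tied to a year, a group of participants or an amendment. The recruitment section covers both the 2009 and 2010 intakes and then gives a single supply rule, so the text does not support reading the two figures as one per year.

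What is at stake is the amount of trial product issued and the safety justification for it. The margin above 100 is claimed for about 5 ml and 3 ml a day only. Staff who follow the recruitment section would give a six-year-old three times the amount for which any margin is stated. Participants may also use the lotion in the daytime, so the volume issued is a relevant upper limit on average use. Replacement lotion may be handed out by village health volunteers during the rains (Follow-up Surveys), and they need one clear quantity for each age group.

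**Working it through.** **1. Daily amounts, taking 30 days to the month.**

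- Interventions, adults: 3 × 50 / 30 = 5.0 ml/day, as stated.
- Interventions, under 12: 2 × 50 / 30 = 3.33 ml/day. The 50 ml bottle is carried over from the adult sentence, and the stated figure of about 3 ml supports this.
- Recruitment and Baseline Survey: 3 × 100 / 30 = 10.0 ml/day, as stated.

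Each section agrees with its own arithmetic, so the conflict is not one mistyped digit.

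**2. Ratios.** Adults: 10 / 5 = 2.0. Under 12: 10 / 3.33 = 3.0.

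**3. Carrying the stated margin over.** The margin is NOEL divided by exposure. If exposure is proportional to the amount applied, the lower bound of 100 rescales as follows:

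- adults: 100 × 5 / 10 = 50;
- under 12: 100 × 3.33 / 10 = 33 (or 30 if 3 ml is used).

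This step needs no body weight, NOEL or absorption figure, only that the absorbed fraction does not change with the amount applied. The results are rescaled lower bounds, not estimates of the margin.

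**4. Illustration of absolute margins.** The formula is margin = NOEL × body weight / (ml/day × 150 mg/ml × absorbed fraction).

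- From the protocol: 15% DEET; 5–8% absorbed; NOEL 200 mg/kg (acute) and 500 mg/kg/day (chronic).
- Assumed: lotion density 1 g/ml (hence 150 mg/ml), an absorbed-dose basis, and the body weights shown.

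Worked case, 20 kg child at 10 ml/day: 1,500 mg applied; 75–120 mg absorbed; 3.75–6.0 mg/kg. Acute margin 200/3.75 to 200/6.0 = 53 to 33. Chronic margin 500/3.75 to 500/6.0 = 133 to 83.

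In the table the first figure of each pair is for 5% absorption and the second for 8%.

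| Assumed weight | ml/day | Acute margin | Chronic margin |
|---|---|---|---|
| Child 15 kg | 3.33 | 120–75 | 300–188 |
| Child 20 kg | 3.33 | 160–100 | 400–250 |
| Child 30 kg | 3.33 | 240–150 | 600–375 |
| Child 15 kg | 10 | 40–25 | 100–63 |
| Child 20 kg | 10 | 53–33 | 133–83 |
| Child 30 kg | 10 | 80–50 | 200–125 |
| Adult 40 kg | 5 | 213–133 | 533–333 |
| Adult 60 kg | 5 | 320–200 | 800–500 |
| Adult 40 kg | 10 | 107–67 | 267–167 |
| Adult 60 kg | 10 | 160–100 | 400–250 |

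At the Interventions amounts this broadly reproduces the protocol's claim of a margin above 100, except for the lightest children at the higher absorption. At 10 ml/day the acute margin is below 100 for every child weight shown. An acute margin of 100 at that amount needs a body weight of 1,500 × 0.05 × 100 / 200 = 37.5 kg at 5% absorption, or 1,500 × 0.08 × 100 / 200 = 60 kg at 8%.

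**5. Dependence on the dose basis.** The protocol does not say whether its margins use applied or absorbed dose. On applied dose, even 5 ml/day in a 60 kg adult gives 750 / 60 = 12.5 mg/kg and an acute margin of 200 / 12.5 = 16. The absolute margins therefore depend on the basis; the ratios 2.0 and 3.0 do not.

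**The case against.** The best defence accepts the contradiction and disputes its weight.

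- **The comparison of arms is unaffected.** Both arms receive the same supply, so randomisation, blinding, outcome and analysis do not change. This stands. The point concerns product supply and safety, not bias.
- **Supply is not dose.** The larger figure allows for 10 ml a day without instructing it, and staff demonstrate how much to apply. This also stands, so the margins at 10 ml/day describe full use of what is issued. Daytime use is not peculiar to the recruitment section either, since Interventions permits it too.
- **The safety picture is more reassuring than one sentence suggests.** DEET Safety also cites reviews that found DEET safe when used appropriately and could not establish it as the cause of seizures. Under-sixes are excluded, and side effects are recorded. This is fair context, but none of it supplies a margin for 10 ml/day in a child.
- **The numerical shortfall lies mainly with light participants.** For adults the chronic margin stays above 100 at 10 ml/day, and the acute margin depends on weight and absorption. This stands.
- **The smaller amounts are not beyond question.** At an assumed 15 kg and 8% absorption the under-12 acute margin is 75. This also stands, and it is a reason to check the lightest children whichever supply is kept.

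None of these points says which supply governs, or extends the stated margin to the larger one.

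**Conclusion.** The concern holds. The protocol contradicts itself on the lotion supply, by a factor of 2.0 for adults and 3.0 for children under 12, and its safety statement covers only the smaller amounts. The ratios rest on the protocol's own figures, with 50 ml bottles assumed for under-12s. The rescaled bounds of 50 and 33 also assume a constant absorbed fraction. The absolute margins rest on assumed body weights, density and an absorbed-dose basis, and are illustrations only.

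Harm at 10 ml a day is not shown. This still has to be corrected, because the document does not fix how much product a child receives and one of its two answers has no stated safety support.

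**What to change.** State one monthly supply by age group and use it in both Interventions and Recruitment and Baseline Survey. There are two ways to do this.

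1. **Keep the Interventions amounts.** Change the recruitment section to three 50 ml bottles for adults and two 50 ml bottles for under-12s. This is a wording correction in one section. A short confirmation of the margin for the lightest six-year-olds would be prudent.
2. **Keep 10 ml a day.** Set a separate child quantity. Then recompute and state the acute and chronic margins for the lightest eligible participants at the amounts supplied, saying whether applied or absorbed dose is used. This adds a short calculation.

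The clinical and toxicology leads should decide which quantity is right. Labels and operating procedures should be aligned with the decision. The starting volume for the check of lotion left in returned bottles (Quality Control and Assurance) should match as well, although no stated analysis depends on it.
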